#### Statistical analyses

Continuous data will be compared using Student’s t test or Mann–Whitney U test, and categorical data will be compared using Pearson’s χ^2^ or Fisher’s exact tests, as appropriate. Mixed linear models will be used to evaluate the development of antibody and T cell immunity towards VZV over time and to explore risk factors for non-response.

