#### Secondary aims

The anti-glycoprotein E antibody response rate and risk factors for anti- glycoprotein E antibody non-response.

The persistence of anti-glycoprotein E antibody and T cell immune responses.

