### Antibody assay

The anti-glycoprotein E antibody response rate will be determined by Enzyme-Linked Immunosorbent Assay (ELISA). Glycoprotein E is the main target for VZV-specific immune responses [24]. We will establish and validate a previously reported ELISA and measure anti-glycoprotein E antibody concentrations in plasma samples collected from all participants at all time points. The anti-glycoprotein E antibody response rate will be defined as the percentage of subjects with anti-glycoprotein E antibody concentration ≥ 4-fold higher than at baseline.

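### Linear mixed models are named for risk factors for non-response, although antibody response is defined as a yes/no outcome; confidence intervals for those risk factors can be mis-sized

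*Protocol article*

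**What the plan says.** Three statements in the protocol article bear on this point.

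- **Secondary aims** lists "The anti-glycoprotein E antibody response rate and risk factors for anti- glycoprotein E antibody non-response".
- **Antibody assay** defines the response rate as the "percentage of subjects with anti-glycoprotein E antibody concentration ≥ 4-fold higher than at baseline". At the level of the participant this is a yes/no variable.
- **Statistical analyses** names one regression method: "Mixed linear models will be used to evaluate the development of antibody and T cell immunity towards VZV over time and to explore risk factors". The sentence thus gives the model two tasks, and the second reads in full "to explore risk factors for non-response".

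The preceding sentence says that "categorical data will be compared using" Pearson's chi-square or Fisher's exact test. No logistic or other binary-outcome regression is named. No cut-off is given for T cell non-response.

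**The concern.** A linear mixed model suits a continuous antibody or T cell measure followed over time, which is the first task in the sentence. It does not suit the second task if non-response means failing the 4-fold threshold. For a 0/1 variable the variance is p(1 − p), so it changes with the risk itself, whereas the standard linear mixed model assumes one residual variance for everyone. When a risk factor is unevenly distributed and changes the risk, the model's standard error is then wrong, and so is the width of the confidence interval.

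The named alternatives do not fill the gap. Chi-square and Fisher tests compare groups without adjustment, so they cannot separate correlated risk factors or use several visits per participant.

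At stake is which factors are reported as linked to non-response, and with what precision. The Discussion suggests that identified risk factors could inform surveillance and the possible need for boosters.

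**Working it through.** The plan states no power, alpha or effect size for this aim, so there is no figure of its own to reproduce. The check asks how far a constant-variance standard error can depart from the correct one.

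**Inputs from the protocol (Sample size section).** 375 waiting-list candidates, and recipients in strata of 250, 125 and 125. Recipients: 250 + 125 + 125 = 500. Total: 500 + 375 = 875. One stratum of 125 against the other 750 is a contrast that the design invites.

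**Assumed inputs.** Non-response rates and, in the table, the share exposed. The protocol gives neither.

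**Formulas.** One binary risk factor, one visit, group sizes n0 and n1, non-response risks p0 and p1:

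- pooled variance s² = [n0·p0(1 − p0) + n1·p1(1 − p1)] / (n0 + n1)
- model SE = √[s²(1/n0 + 1/n1)]
- true SE = √[p0(1 − p0)/n0 + p1(1 − p1)/n1]
- coverage of a nominal 95% interval = 2Φ(1.96 × model SE / true SE) − 1

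**Unbalanced case: 10% in 750, 40% in 125.**

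- s² = (750 × 0.09 + 125 × 0.24)/875 = 97.5/875 = 0.1114
- model SE = √[0.1114 × (1/750 + 1/125)] = 0.0323
- true SE = √(0.09/750 + 0.24/125) = √0.00204 = 0.0452
- ratio = 0.71; coverage about 84%. Simulation of the same case gave 83%.

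**Same rates on the main split: 10% in 375 candidates, 40% in 500 recipients.**

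- s² = (375 × 0.09 + 500 × 0.24)/875 = 153.75/875 = 0.1757
- model SE = √[0.1757 × (1/375 + 1/500)] = 0.0286
- true SE = √(0.09/375 + 0.24/500) = √0.00072 = 0.0268
- ratio = 1.07; coverage about 96%

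**Range over other assumed rates (total 875).**

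| Non-response, unexposed vs exposed | Share exposed | Model SE / true SE | Coverage |
|---|---|---|---|
| 2% vs 15% | 10% | 0.51 | 68% |
| 5% vs 20% | 20% | 0.71 | 84% |
| 10% vs 30% | 20% | 0.78 | 88% |
| 20% vs 40% | 20% | 0.89 | 92% |
| 30% vs 50% | 20% | 0.95 | 94% |
| 40% vs 60% | 20% | 1.00 | 95% |
| 10% vs 30% | 50% | 1.00 | 95% |
| 5% vs 20% | 80% | 1.40 | 99% |

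Intervals are too narrow when a less common exposure carries the higher risk and non-response is uncommon. They are too wide when the common exposure carries the higher risk. The error vanishes with equal groups, or when the two risks lie symmetrically around 50%.

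**No effect.** If p0 = p1, the two variances are equal and the two standard errors coincide (ratio 1.00). For a single factor, p-values under the null are therefore close to nominal.

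This is a single-visit calculation with the usual constant-variance error. It shows the mechanism and the direction; it is not a forecast for the full repeated-measures model.

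**The case against.** The strongest reply is that the protocol does not say the 0/1 indicator is the dependent variable. The sentence can be read as covariates in a linear mixed model of the continuous measure, which is a legitimate way to find factors linked to a poor response. The 4-fold rule is given for the response rate, and elsewhere the article speaks more broadly of immune non-response. On this view the link and dependent variable are details for a fuller document. That reading is available, but it does not rescue the wording: an analysis of continuous concentration addresses how large the response is, whereas the secondary aim concerns non-response and the only definition given is a threshold. The article did not leave the method open; it named one.

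Other parts of the reply stand and limit the point.

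- A reader might infer that intervals and p-values are bound to be wrong. The documents do not support this. They give no non-response rates, several plausible settings give 94% to 96% coverage, and simulation of the 750/125 split with no effect gave a type I error of 4.9% to 5.1%. It rose to 6% to 7% only when the tested factor was correlated (0.3 to 0.5) with another strong risk factor.
- A reader might infer that impossible fitted probabilities would undermine guidance on surveillance or boosters. The Discussion speaks of identifying risk factors, not of predicting individual risk, so fitted values below zero affect no stated use.
- A reader might infer a loss of power from analysing raw rather than log-transformed concentrations. No scale is stated, raw-scale analysis would be an assumption, and transformation is commonly left to an analysis plan.
- A robust variance would repair the standard errors even with a linear model.
- An unadjusted comparison of responders and non-responders already has suitable tests.

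**Conclusion.** The point holds as a mismatch between the stated outcome and the stated model. Response is defined as yes/no, its risk factors are a secondary aim, and the only regression named for them is a linear mixed model. If that model is fitted to the 0/1 outcome with constant variance, confidence intervals for risk-factor effects can be mis-sized. Coverage is about 84% for 10% in 750 versus 40% in 125. It is as low as 68% for a rarer exposure with very low background non-response, and about 95% to 96% with more balanced groups or non-response near 50%. All of these figures rest on assumed rates.

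Severity is moderate. The study describes itself as descriptive and exploratory, and the point concerns one secondary aim. It changes neither the sample size nor the data collected, and it can be settled before analysis.

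**What to change.** Amend the Statistical analyses section in one of two ways.

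1. **Keep non-response as the outcome.** Analyse it with a binary-outcome model: logistic regression at a fixed, named post-vaccination visit, or a mixed logistic model or GEE if several visits are used. Keep linear mixed models for continuous antibody and T cell measures over time.
2. **Keep the linear mixed model for risk factors.** State that its dependent variable is the continuous antibody concentration, adjusted for baseline, and call the outcome magnitude of response rather than non-response, in the secondary aim as well.

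The first option matches the aim and the response definition as they now stand. Either costs one or two sentences, with no extra samples, visits or participants.

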## Discussion

Kidney transplant recipients are at higher risk of herpes zoster than immunocompetent individuals [7–9] and at increased risk of severe herpes zoster disease and post-herpetic neuralgia [9–11]. Current international and Danish guidelines recommend RZV vaccination of kidney transplant candidates prior to transplantation [17, 18]. However, evidence on the robustness and duration of the immune response, as well as the optimal timing of vaccination is warranted. Through a characterization of the VZV specific immune response in kidney transplant candidates and recipients, this study has the potential to improve preventive strategies against herpes zoster in a population at risk. By observing immune responses in kidney transplant candidates and recipients vaccinated at different time points with regards to transplantation we expect to be able to establish the most optimal timing of vaccination for kidney transplant candidates and recipients. Furthermore, identification of risk factors for immune non-response could provide guidance for increased surveillance of individuals at higher risk of herpes zoster and a potential need for additional RZV booster doses.

## Data Availability

The datasets generated and/or analyzed during the current study are not publicly available due privacy regulations but are available from the corresponding authors on reasonable request.

## Abbreviations

HINT: Herpesvirus Infections in Kidney Transplant Patients Study
VZV: Varicella zoster virus
HZ: Herpes zoster
RZV: Adjuvanted recombinant glycoprotein E subunit herpes zoster vaccine
ELISA: Enzyme-Linked Immunosorbent Assay
PBMC: Peripheral blood mononuclear cells
pMHC: Peptide-Major Histocompatibility Complex
HLA: Human leukocyte antigen
TCR: T cell receptor
DDV: The Danish vaccination register
MiBa: The Danish microbiology database
